### Data Processing and Quality Control

The data will be recorded on case report forms previously designed for that purpose. After completing the case report form, the monitor of the study will review the data to confirm completeness, readability, accuracy, and consistency. All detected errors will be reported, evaluated, and properly corrected by the originator of the forms. All corrections will be noted with dates and initials of the person issuing the correction in accordance with the World Health Organization’s Guidelines for Good Clinical Practice [38]. Immediately after the form is correct, the information will be recorded in a database.

### Production and Purification of Viral Vectors

We will produce the AAV1, AAV2, and AAV9 vectors using the cotransfection strategy of human embryonic kidney 293 cells specially modified to facilitate transfection of AAV (AAV-293; Agilent Technologies, Santa Clara, CA, USA; catalog #240073) via calcium phosphate (ThermoFisher Scientific, Waltham, MA, USA) [39]. We will use a pAAV with the plasmid of interest, a helper adenoviral plasmid, and a chimeric construct having the AAV2 *rep* gene, along with the corresponding AAV1, AAV2, or AAV9 *cap* gene [9].

We will evaluate the AAV-293 cells for microbial contamination using the polymerase chain reaction protocol for detecting mycoplasma. Following the previously described protocol, 2 days after transfection, we will collect cells and purify the vector particles using precipitation gradient centrifugation methods. The harvested cells will be lysed by successive cycles of freezing, thawing, and sonication, then treated with Benzonase nuclease (Novagen, Madison, WI, USA) and deoxycholic acid (Sigma-Aldrich, St. Louis, MO, USA), and then subjected to 3 successive rounds of cesium chloride density-gradient ultracentrifugation (ThermoFisher Scientific). We will collect the fractions containing AAV vector, concentrate it using 1-mmol/L MgCl_2_(phosphate buffered saline) (Gibco, BRL), and store it at –80°C until use. Quantification of AAV1, AAV2, or AAV9-cytomegalovirus-luciferase (in viral genomes/mL) vectors will be determined by quantitative real-time polymerase chain reaction probes using SYBR Green Supermix (Bio-Rad, Hercules, CA, USA) and primers specific for luciferase complementary DNA. The forward and reverse primers that we will use are CCCACCGTCGTATTCGTGAG5'-3' and 5'TCAGGGCGATGGTTTTGTCCC-3', respectively.

Typically, we have managed to standardize the protocol and achieve titers in the range of 2×10^12^ to 5×10^12^ viral genomes/mL. To generate standard curves, we will use a plasmid of known copy numbers corresponding to the vectors used to generate AAV vectors carrying the appropriate complementary DNA. Viral vectors will be produced in collaboration with the laboratory of the Department of Gene Therapy and Regenerative Medicine, Free University of Brussels, by the principal investigator, [name].

### Determination of Neutralizing Antibodies

We will determine NAb titers against serotypes AAV1, AAV2, and AAV9 following the recently published protocol in *Human Gene Therapy Methods* by Dr F Mingozzi’s group [37]. This protocol is used due to high reproducibility of the results, in addition to the efficiency and safety it offers. Determination of NAb titers is based on an AAV vector expressing a reporter gene, which is incubated with the sample to be evaluated before *in vitro* transduction of a specific cell line. We describe the main features of the protocol below; for a more detailed protocol please review the publication by Meliani et al [37].

### Multiplicity of Infection Selection

Importantly, as Meliani et al [37] mention, an optimal multiplicity of infection (MOI) should be determined for each serotype. We will select the MOI for each serotype NAb assay by determining the viral vector needed to give a luciferase signal above background signal and below saturation levels, measured in relative light units, considering that the number of AAV genome copy particles to be used is equal to the desired MOI multiplied by the number of cells to be infected.

For our project, we will transduce human embryonic kidney 293-derived 2V6.11 cells with an increasing MOI of the corresponding serotype (AAV1, AAV2, or AAV9); 24 hours later we will measure luciferase expression and select the most appropriate MOI for each serotype.

### Assay Validation

Validation of any assay is fundamental before translation to clinical practice. Simultaneously with execution of the project and, based on initial results from the patients’ samples, we will perform a process similar to the following (to be reported in the final paper): 1) determine the optimal cut point (threshold), 2) determine sensitivity, 3) select quality controls, 4) set specificity and assay precision, and 5) determine selectivity. We refer the reader to previously published papers for more detailed information [40,41].

After selecting the desired MOI and establishing the conditions of the assay, we will conduct a 4-day NAb assay protocol, as follows.

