## Results

We have completed the first phase of the project. During this stage, all the documents necessary for recording and storing information have been elaborated and submitted to the ethical committee of the FCV for approval. We expect to begin recruiting patients in the spring of 2016. We expect to complete the second phase, in which we will validate all the protocols for the project—including determining the titer of the viral vectors, selecting the MOI that we will use for each serotype, and validating the assay—by the end of 2016. Finally, we will conduct the third phase, in which we will analyze serum samples from patients and healthy volunteers, during 2017. We expect to have the first results in mid-2017.

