## Discussion

For this project, we will evaluate anti-AAV1, -AAV2, and -AAV9 NAbs by using the *in vitro* transduction inhibition assay, to determine the presence, activity, and titers of NAbs in patient sera. Several critical steps and validation of the protocol should precede analysis of the patient samples (eg, selection of MOI, selection of the cells to be used during the assay). We expect that the final results may indicate the seroprevalence of NAbs for the selected serotypes and allow for comparison with previously reported results from other populations. The causes of the demonstrated high variability between the evaluated populations continue to be debated, and more studies including different healthy populations and under specific pathologic circumstances need to be conducted worldwide. Importantly, the method of determination should be standardized to obtain more reliable and comparable data. Recent reports support the higher sensitivity of intramuscular *in vivo* assays to determine NAb response [42], suggesting that *in vivo* NAb assays are more sensitive than *in vitro* assays for determining inclusion and exclusion criteria in clinical trials; however, the technical difficulties and higher cost associated with using *in vivo* assays in population studies mean that *in vitro* assays still have an important function.

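### The assay cut point is to be set from the study's own early patient samples, against the article's statement that validation comes first, and no titer is named in advance as NAb-positive

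*Protocol article*

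**What the plan says.** Three places in the protocol article bear on the order of work.

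- **Methods, Assay Validation.** The work is to be done "Simultaneously with execution of the project and, based on initial results from the patients’ samples". Its content is listed as "1) determine the optimal cut point (threshold), 2) determine sensitivity, 3) select quality controls, 4) set specificity and assay precision, and 5) determine selectivity". The procedure is described only as resembling this list, with the details promised for the final paper.
- **Results.** The second phase covers "selecting the MOI that we will use for each serotype, and validating the assay—by the end of 2016". After that, "we will conduct the third phase, in which we will analyze serum samples from patients and healthy volunteers, during 2017". Recruitment is expected to start in spring 2016.
- **Discussion.** "Several critical steps and validation of the protocol should precede analysis of the patient samples".

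Two further places bear on what the cut point does. The Objective names the prevalence of NAbs against AAV1, AAV2 and AAV9 as the goal. The Day 4 section fixes how a titer is read (at least 50% inhibition of luciferase expression) but does not say which titer counts as positive.

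**The concern.** A prevalence needs a rule that sorts each participant into positive or negative. The Day 4 rule gives a titer and stops there. The only threshold the article announces beyond that is the cut point in Assay Validation, and its source is early results from the patients whose prevalence is to be estimated.

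Two things are at stake. First, the estimate depends on a choice made after seeing part of the data, and the usual confidence interval for a proportion does not carry the uncertainty of that choice. Second, specificity needs samples known to be negative. The patients' serostatus is what the study sets out to find. The Introduction cites seropositivity of 30% to 80% in other populations, so early patient samples cannot be taken as a negative set.

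**Working it through.** **1. Order of work, side by side**

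| Section | Samples used for validation | Timing |
|---|---|---|
| Assay Validation | early patient samples | while the project runs |
| Discussion | not stated | before patient samples are analyzed |
| Results | not stated | done by end of 2016; study sera in 2017 |

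Validation that rests on patient results cannot also precede the analysis of patient samples, so the first two rows contradict each other. The third row is a weaker conflict. Patients recruited from spring 2016 could supply sera for validation in 2016, but the article does not say so, and it places the analysis of patient sera in the later phase.

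**2. How much the positivity titer matters**

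The article derives no figure that could be reproduced; its 60 + 60 participants are a convenience size. What follows is an illustration.

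Inputs from the article: n = 60 per group (Study Population), half-log dilutions starting at 1:1 (Table 1), and 30% to 80% as the cited range of seropositivity (Introduction).

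Assumed: log10 titers are normal with SD 0.75, 1.0 or 1.5, and the proportion p at or above 1:1 is 30%, 60% or 80%.

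Sampling error: half-width = 1.96 × √(p(1−p)/60).
- p = 0.30: 1.96 × √(0.21/60) = 11.6 points
- p = 0.60: 1.96 × √(0.24/60) = 12.4 points
- p = 0.80: 1.96 × √(0.16/60) = 10.1 points

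Effect of one step, from 1:1 to 1:3.16 (0.5 on the log10 scale): the mean is μ = SD × Φ⁻¹(p), and the new prevalence is 1 − Φ((0.5 − μ)/SD). For example, with p = 0.60 and SD = 0.75, μ = 0.190, (0.5 − 0.190)/0.75 = 0.413, and the new prevalence is 34.0%, a drop of 26.0 points.

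| Positive at 1:1 | Drop, SD 0.75 | Drop, SD 1.0 | Drop, SD 1.5 | Half-width |
|---|---|---|---|---|
| 30% | 18.3 | 14.7 | 10.4 | 11.6 |
| 60% | 26.0 | 19.7 | 13.2 | 12.4 |
| 80% | 23.1 | 16.6 | 10.6 | 10.1 |

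In eight of the nine cases one step exceeds the sampling half-width; in the ninth it is slightly smaller.

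**3. Effect on the comparison of the two groups**

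Simulation with identical groups of 60 (20,000 runs; log10 titer mean 0.7, SD 1.2, plus other assumed distributions). If the cut point is taken from the patients alone, as the mean + 1.645 SD or the median of the first 10, 20, 30 or all 60, the chi-square test rejects in about 3% to 5.5% of runs, so it is not inflated. A rate of about 20% arises only if someone searches six cut points for the one that best separates patients from volunteers.

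**The case against.** **Early samples may simply feed the second phase.** Recruitment starts in spring 2016, so some patient sera could be run during validation, and the remaining sera could be read later under a fixed assay. This eases the conflict with the calendar in Results. It does not reconcile Assay Validation with the Discussion. Nor does the article say that those sera stay out of the 60, or that the cut point is locked before the rest are read.

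**The 50% inhibition rule might seem to contradict the cut point.** A reader might infer that the Day 4 rule already fixes the threshold, so that the sections cannot all hold. That goes too far. The rule governs how a titer is read, and a separate cut point for positivity can coexist with it. What is missing is the statement of which titer is positive.

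**A reader might infer false positives in the comparison of patients with volunteers.** The article does not support this. Inflation to about 20% needs a search over both groups' data, and no section describes one. The patient-only rules tried here show none.

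**The bias has no stated direction.** This objection stands. The article does not define what makes a cut point optimal, so neither over- nor underestimation can be asserted.

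**Details may be in a fuller protocol or analysis plan.** They may be, and leaving them there is no fault. But the article makes a definite statement about which samples are used and when, and contradicts it elsewhere.

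**Conclusion.** The concern holds in this form: the sections conflict on the order of validation and sample analysis, and the positivity threshold is left to be set from study patients of unknown serostatus. The contradiction rests on the text alone.

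Its size rests on assumptions. With normal log10 titers and SDs of 0.75 to 1.5, one half-log step shifts prevalence by about 10 to 26 points, against a half-width of 10 to 12 points. The choice of threshold can thus matter as much as sampling error or more, and the reported interval would not show it. These figures show how sensitive prevalence is to the threshold; they do not estimate a bias. No claim is made about the direction of bias or about the type I error of the chi-square test.

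**What to change.** - In Assay Validation, delete the words that base the work on early patient results, and state one order that agrees with Results and the Discussion.
- Set the MOI, cut point, precision and controls in the planned second phase, on control sera or other sera from outside the 60 + 60 participants.
- Before any study sample is read, state which titer under the 50% inhibition rule counts as NAb-positive, for each serotype, and lock it. Keeping the 50% rule alone does not close the gap.
- Report prevalence at any cut point derived from study samples only as a labelled sensitivity analysis.

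**Cost.** Wording changes and a small number of control sera in a phase that is already planned. The number should not be too small if the cut point is estimated from them. In simulation with normal readings, a mean + 1.645 SD cut point aimed at 5% false positives has a true rate with a 95% range of 0.5% to 26% from 10 negative sera, 1% to 17% from 20, and 1.4% to 14% from 30. Given the financial limits stated under Study Population, the number should be chosen and stated with this in view.

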#### Day 1: Cell Culture 2V6.11

We will suspend 2×10^4^ 2V6.11 cells in 100 μL of Dulbecco’s modified Eagle’s medium (DMEM)/Ham’s nutrient mixture F-12 culture medium (Sigma-Aldrich) supplemented with 10% fetal bovine serum. The cells will be cultured for 24 hours in an incubator (37°C, 5% CO_2_) in 96-well culture plates. To induce expression of the *E4* gene, Ponasterone A will be added to the culture medium (Sigma-Aldrich) (10 mL).

#### Day 2: Sample Controls and AAV Vector Preparation

For transduction, we will prepare serial dilutions of 10 mL of patient serum and a control sample using fetal bovine serum as the diluent (Table 1). One control sample will correspond to 100% transduction of the vector and another to 0% transduction of the vector to allow for determining the background luminescence signal. The viral vector will be diluted to the concentration selected (according to the desired working MOI) in DMEM without the use of fetal bovine serum. Subsequently, we will add 20 μL of the vector to each of the sample dilutions and controls. These samples will be grown for 1 hour at 37°C and, subsequently, 7.5 μL of each neutralized sample will be added to the cell culture medium. Cells will remain in overnight incubation at 37°C and 5% CO_2_.

**Table 1 table1:** Example^a^ of half-log dilution preparation for the test sample and control using fetal bovine serum as the diluent before being mixed with the viral vector (20 μL) and added to 96-well plated cultured cells.

Dilution no.	Relation	Volume (μL) of sample/control	Volume (μL) of diluent
1	1:1	40	0
2	1:3.16	12 of dilution 1	26
3	1:10	12 of dilution 2	26	
4	1:31.6	12 of dilution 3	26
5	1:100	12 of dilution 4	26
6	1:316	12 of dilution 5	26
7	1:1000	12 of dilution 6	26
8	1:3160	12 of dilution 7	26

^a^Modified from Meliani et al [37].

#### Day 3: Cell Lysis and Measurement of Luciferase Activity

On this day, we will use the protocol for the Bright-Glo Luciferase Assay System (Promega Corporation, Madison, WI, USA). After incubating the assay for 15 minutes at room temperature, we will add 100 μL of cell lysis medium and the luminescence substrate, then wait for 3 minutes until lysis is complete. Luminescence will be measured using the EnSpire reader (PerkinElmer, Inc, Waltham, MA, USA).

#### Day 4: Determination of Anti-AAV NAb titers

To calculate the luciferase expression percentage (LEP) and luciferase inhibition percentage (LIP), we will use the formulas LEP=[(test sample luciferase reading−no virus luciferase signal)/(maximum luciferase signal−no virus luciferase signal)]×100 and LIP = 100 – LEP.

The neutralizing titer of the sample is reported as the first dilution at which ≥50% inhibition of luciferase expression is measured. For example, if ≥50% inhibition is observed at a sample dilution of 1:10, then the neutralizing titer is reported as 1:10. NAb titers will be determined for the selected serotypes in collaboration with the laboratory of the Department of Gene Therapy and Regenerative Medicine at the Free University of Brussels by the principal investigator, [name].

### Statistical Analysis

We will describe data from all measurements of continuous variables using measures of central tendency such as means and standard deviations, considering the coefficients of variation between replicates (3) of the experiments. We will report counts and proportions of categorical variables with their respective 95% confidence intervals. For tests between study groups, we will use analysis of variance to assess differences between means and the chi-square test for differences between proportions. Differences with a value of *P*<.05 will be considered significant. We will use Stata 8.0 statistical software (StataCorp LP).

## Results

We have completed the first phase of the project. During this stage, all the documents necessary for recording and storing information have been elaborated and submitted to the ethical committee of the FCV for approval. We expect to begin recruiting patients in the spring of 2016. We expect to complete the second phase, in which we will validate all the protocols for the project—including determining the titer of the viral vectors, selecting the MOI that we will use for each serotype, and validating the assay—by the end of 2016. Finally, we will conduct the third phase, in which we will analyze serum samples from patients and healthy volunteers, during 2017. We expect to have the first results in mid-2017.

## Discussion

For this project, we will evaluate anti-AAV1, -AAV2, and -AAV9 NAbs by using the *in vitro* transduction inhibition assay, to determine the presence, activity, and titers of NAbs in patient sera. Several critical steps and validation of the protocol should precede analysis of the patient samples (eg, selection of MOI, selection of the cells to be used during the assay). We expect that the final results may indicate the seroprevalence of NAbs for the selected serotypes and allow for comparison with previously reported results from other populations. The causes of the demonstrated high variability between the evaluated populations continue to be debated, and more studies including different healthy populations and under specific pathologic circumstances need to be conducted worldwide. Importantly, the method of determination should be standardized to obtain more reliable and comparable data. Recent reports support the higher sensitivity of intramuscular *in vivo* assays to determine NAb response [42], suggesting that *in vivo* NAb assays are more sensitive than *in vitro* assays for determining inclusion and exclusion criteria in clinical trials; however, the technical difficulties and higher cost associated with using *in vivo* assays in population studies mean that *in vitro* assays still have an important function.

### Conclusion

We expect to have preliminary results, including the titer of the viral vectors, the MOI that we will use, and test assay validations, at the end of 2016. The results of this study will become the initial step for bigger population studies to characterize our population and provide the necessary epidemiological information for clinical trials using AAV in Latin America.

## Abbreviations

AAV: adeno-associated virus
CUPID: Calcium Upregulation by Percutaneous Administration of Gene Therapy in Cardiac Disease
CVD: cardiovascular disease
ELISA: enzyme-linked immunosorbent assay
FCV: Cardiovascular Foundation of Colombia
HF: heart failure
LEP: luciferase expression percentage
LIP: luciferase inhibition percentage
MOI: multiplicity of infection
NAb: neutralizing antibody
SERCA2a: sarcoplasmic reticulum Ca2+-ATPase
